### 12.3 Sample size calculation

This trial is powered as a Fleming's single stage phase II trial of the intervention arm. The main endpoint is the proportion of patients completing a pre-determined level of compliance to the recommended NMES programme (NMES for 30min three times a week) measured using a self-report daily diary. Following advice from the cachexia subgroup of the NCRI Palliative Care Clinical Studies Group we have determined that 80% of patients should adhere to this minimum level in order to warrant a future phase III study. Conversely, if  $\leq 50\%$  adhered to this minimum level, this would give grounds to reject further study. Using a Fleming's one stage method, 20 patients will be required to distinguish between these rates (90% power,  $p=0.05$ ) and if  $\geq 15$  out of 20 patients adhere, this would warrant further investigation.

We have included a randomised control arm into this trial design in order to allow comparison of some secondary end points. Originally the trial started by randomising with a 1:1 allocation; however this was changed to a 2:1 in favour of the NMES arm allocation part way through the trial in order to support recruitment. As the study analysis is based on a within-intervention arm analysis, the statistical integrity of the study is not affected. A local audit suggests about 25% of patients drop out before reaching 3 cycles. We

require 20 patients in the treatment arm to be available for analysis; therefore we estimate that 26 patients need to be recruited to this arm. At the time of the change in the randomisation allocation ratio this meant that 47 patients would need to be recruited in total (26 to the treatment arm and 21 to the control arm).

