## **12.5 Statistical analyses**

A full statistical analysis plan will be developed before the first interim analysis of the trial data.

For the primary endpoint, the proportion (and 90% confidence interval) of patients completing NMES for 30min three times a week will be reported.

For the secondary (intention to treat) analyses, change in leg muscle strength from baseline will be compared between trial arms at 9, 17 and 20 weeks.

Descriptive statistics will then be presented for the following measures at 9, 17 and 20 weeks:

- Change in QoL score from baseline
- Change in body composition from baseline
- Change in nutritional intake from baseline
- Change in fatigue from baseline

Response to chemotherapy at 9 and 12 weeks will be described in each trial arm.

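### Section 12.3 recruits 26 where its own inputs give 27, states its go rule for a denominator of exactly 20 only, and at 20 that rule has about 80% power, not 90%

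*Protocol*

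**What the plan says.** Protocol section 12.3 sizes the NMES arm as a Fleming single-stage design. The target is set so that "we have determined that 80% of patients should adhere to this minimum level", and if 50% or fewer "adhered to this minimum level, this would give grounds to reject further study". It then states that "20 patients will be required to distinguish between these rates (90% power", p=0.05), and that 15 or more "out of 20 patients adhere, this would warrant further investigation". No other cut-off appears.

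The allowance for attrition follows in the same section: "A local audit suggests about 25% of patients drop out before reaching 3 cycles"; the trial will "require 20 patients in the treatment arm to be available for analysis"; "therefore we estimate that 26 patients need to be recruited to this arm".

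Section 12.5 adds that "the proportion (and 90% confidence interval) of patients completing NMES for 30min three times a week will be reported", and defers a full analysis plan, which is not shown. Section 12.2.1 counts missing diary data as non-compliance. Section 11.3 withdraws participants whose chemotherapy stops after one or two cycles.

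**The concern.** Three things in section 12.3 do not fit together.

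- **Recruitment figure.** Inflating 20 for 25% drop-out does not give 26. The figure has been rounded down, so on its own inputs the plan expects fewer than the 20 it requires.
- **Denominator.** The section plans to over-recruit against random attrition, so the number analysed is itself random. The rule nevertheless covers one value of it. The protocol does not say that recruitment continues until 20 are evaluable, or that only the first 20 count.
- **Power.** The 90% attached to 15 of 20 does not survive an exact check.

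The rule is the basis for recommending a phase III trial. If the threshold for the realised denominator is chosen after the adherence data are known, in an open trial, the choice can be questioned. If the stated power is too high, a no-go result will be read as firmer evidence against NMES than it is.

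**Working it through.** **Inputs (section 12.3).** p0 = 0.50; p1 = 0.80; alpha 0.05, sidedness not stated; power 90%; n = 20; go if 15 or more; drop-out about 25%; recruit 26.

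**1. The plan's n of 20.** Normal approximation, one-sided 5%, 90% power:

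n = [(1.645 × √0.25 + 1.282 × √0.16) / 0.30]² = 19.8, rounded up to 20.

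This reproduces the plan. A two-sided 5% level gives 24.8, so 25. One-sided 5% is therefore what the design uses, and it fits the 90% interval in section 12.5.

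**2. The plan's cut-off of 15.** 20 × 0.5 + 1.645 × √(20 × 0.25) = 13.68; nearest integer 14, plus one, is 15. This also reproduces.

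**3. Exact error rates at n = 20.**

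| Rule | P(go) at 0.50 (alpha) | P(go) at 0.80 (power) |
|---|---|---|
| 15 or more of 20 | 2.1% | 80.4% |
| 14 or more of 20 | 5.8% | 91.3% |

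No cut-off at 20 gives both alpha at or below 5% and power of at least 90%. The smallest n that does so exactly is 23 with a cut-off of 16 (4.7%, 92.8%). The approximation in step 1 yields 20; the whole-number cut-off of 15 then gives up about ten points of power.

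**4. Drop-out inflation.** 20/(1 − 0.25) = 26.67, so 27. With 26, the expected number is 26 × 0.75 = 19.5. The figure 26 would be right for a drop-out of 1 − 20/26 = 23.1%.

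**5. Spread of the evaluable number.** Assume drop-outs leave the denominator, as section 12.3 implies, and that the evaluable number is Binomial(26, 0.75). Then P(exactly 20) = 17.8%, P(not 20) = 82.2%, P(20 or more) = 51.5%, P(fewer than 20) = 48.5% and P(17 or fewer) = 18%. Recruiting 27 gives 20.25 expected and P(20 or more) = 64%.

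**6. What happens if the rule is simply carried over.** The protocol specifies neither reading below; they are the two obvious ones.

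| Evaluable | Probability | Count fixed at 15: alpha, power | 75% of n: cut-off, alpha, power |
|---|---|---|---|
| 18 | 13.4% | 0.4%, 50.1% | 14, 1.5%, 71.6% |
| 19 | 17.0% | 1.0%, 67.3% | 15, 1.0%, 67.3% |
| 20 | 17.8% | 2.1%, 80.4% | 15, 2.1%, 80.4% |
| 21 | 15.3% | 3.9%, 89.2% | 16, 1.3%, 76.9% |
| 22 | 10.4% | 6.7%, 94.4% | 17, 0.9%, 73.3% |
| 23 | 5.4% | 10.5%, 97.3% | 18, 0.5%, 69.5% |
| 24 | 2.0% | 15.4%, 98.7% | 18, 1.1%, 81.1% |

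Averaged over all evaluable numbers, the fixed count has alpha 2.9% and power 67.4%; the 75% rule has 1.6% and 74.2%. Re-deriving the cut-off for each n gives 3.3% and 83.8%, with alpha at or below 5% at every n.

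**The case against.** **The shortfall is trivial.** The drop-out rate is given as approximate and 26 as an estimate; 26 is right for 23% drop-out, and moving to 27 raises the expected number by only 0.75. This stands. On its own it is a rounding correction.

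**The analysis plan can set cut-offs for other denominators.** In part this stands. Such cut-offs are often left there, and section 12.5 already promises a summary that works for any denominator: a proportion with a 90% interval. But section 12.3 itself fixes a numerical go rule for a denominator that its own attrition allowance makes unlikely, and attaches a power figure to it. The power figure is wrong whatever the analysis plan says.

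**The decision's error rates are wrong in most outcomes.** A reader might infer this from step 5. The document does not support it. It never says that 15, or 75%, carries over, so away from 20 the error rates are undefined, not shown to be wrong. Even with 15 held fixed, alpha exceeds 5% only at 22 or more evaluable, about 18% of outcomes; the 15.4% at 24 belongs to an outcome with 2% probability. The main loss would be power at 19 or fewer.

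**The stated rates hold at exactly 20.** This too might be inferred from a complaint about other denominators. They do not hold there (step 3).

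**Conclusion.** The point holds in three parts of unequal weight.

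1. The recruitment figure should be 27 for an expected 20. This is minor.
2. The go rule is undefined for about 82% of evaluable numbers, and neither obvious extension keeps the stated properties. It should be settled before the adherence data are examined.
3. The stated 90% power for 15 of 20 is about ten points too high: exact power is 80.4%, so the chance of a no-go when true adherence is 80% is about 20%, not 10%.

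Part 3 uses only figures in section 12.3, with the test read as one-sided. The probabilities in part 2 also assume independent drop-out at exactly 25% and exclusion of drop-outs from the denominator. If instead all 26 were analysed with drop-outs counted as non-compliant, the denominator would not vary, but the 15-of-20 rule would then not apply at all.

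**What to change.** In section 12.3, or there with a pointer to the analysis plan:

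1. State that 26 recruited gives about 19 to 20 evaluable, or that 27 is the figure for an expected 20.
2. State that the test is one-sided and that 15 of 20 has exact alpha 2.1% and power about 80%.
3. Replace the single cut-off with the smallest count whose exact one-sided alpha against 50% is at or below 0.05, with power at 80% adherence:

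| Evaluable | Go if at least | Alpha | Power |
|---|---|---|---|
| 16 | 12 | 3.8% | 0.80 |
| 17 | 13 | 2.5% | 0.76 |
| 18 | 13 | 4.8% | 0.87 |
| 19 | 14 | 3.2% | 0.84 |
| 20 | 15 | 2.1% | 0.80 |
| 21 | 15 | 3.9% | 0.89 |
| 22 | 16 | 2.6% | 0.87 |
| 23 | 16 | 4.7% | 0.93 |
| 24 | 17 | 3.2% | 0.91 |
| 25 | 18 | 2.2% | 0.89 |
| 26 | 18 | 3.8% | 0.94 |

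4. Apply the table to all evaluable NMES-arm participants, not the first 20. Define evaluable and reconcile it with section 12.2.1, so that it is clear who leaves the denominator and who stays in it as non-compliant.

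The cost is a few sentences and a small table, with no extra patients. If the sponsor instead wants an exact 90%, that takes 23 evaluable, or 23/0.75 = 30.7, so 31 recruited to the arm.

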## **12.4 Interim analyses and the role of the Independent Data Monitoring Committee**

Interim analyses of the accumulating data will be performed at regular intervals for review by the Independent Data Monitoring Committee (IDMC). These analyses will be performed by the WCTU.

The IDMC will review the activity, safety and accrual data and, with consideration of any results from any relevant external trials, make a recommendation to the Independent Trial Steering Committee (TSC) on whether the trial should continue recruitment or close to recruitment. While the trial is recruiting, only the appropriate staff at the WCTU and the IDMC will see the results of the interim analyses.

## **12.5 Statistical analyses**

A full statistical analysis plan will be developed before the first interim analysis of the trial data.

For the primary endpoint, the proportion (and 90% confidence interval) of patients completing NMES for 30min three times a week will be reported.

For the secondary (intention to treat) analyses, change in leg muscle strength from baseline will be compared between trial arms at 9, 17 and 20 weeks.

Descriptive statistics will then be presented for the following measures at 9, 17 and 20 weeks:

- Change in QoL score from baseline
- Change in body composition from baseline
- Change in nutritional intake from baseline
- Change in fatigue from baseline

Response to chemotherapy at 9 and 12 weeks will be described in each trial arm.

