### **Secondary:**

- i) Is NMES a safe intervention to offer patients undergoing palliative chemotherapy?
- ii) To what extent does 3 cycles of palliative chemotherapy impact on leg muscle strength, body composition and physical activity levels in patients with NSCLC and can the use of NMES influence these changes?
- iii) What is the rate of recovery or decline in these parameters following cessation of 3–4 cycles of chemotherapy and can the use of NMES influence this?
- iv) What are patients' attitudes about the use of NMES during chemotherapy?

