**17/20 week from start of chemotherapy assessments (3/4 cycles received)**

Quadriceps muscle strength  
Body composition  
Physical activity level  
Nutritional intake  
Fatigue  
Quality of life

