### 9.5 Follow up assessments (17 / 20 weeks from start of chemotherapy)

- Quadriceps muscle strength
- Toxicities
- Body composition
- Physical activity level
- Nutritional intake
- Fatigue
- Quality of life.

A detailed assessment schedule is given in section 9.6 overleaf.

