| NMES                  |                  |        |        |        |        |        |        |        |        |        |         |         |         |            |
| Daily application            |                  |        | X      | X      | X      | X      | X      | X      | X      | X      | X       | X       | X       |            |
| Supervision (home visit)     |                  |        | X      |        |        |        |        |        | X      |        |         |         |         |            |
| Supervision (telephone call) |                  |        |        | X      | X      | X      | X      | X      |        |        | X       | X       | X       |            |
| Adherence assessed           |                  |        |        |        |        |        |        |        |        | X      |         |         | X       |            |
| Interview (subgroup)         |                  |        |        |        |        |        |        |        |        | X      |         |         | X       |            |

*N.B. Serious Adverse Events (SAE) will be collected in real time via a designated SAE fax number.*

*Notes: the timing of assessments will be standardised to treatment cycles and thus will be sufficiently flexible to cope with delays during chemotherapy, e.g. due to neutropenia. The interview is completed either at week 9 or week 12 depending on the patient receiving 3 or 4 cycles of chemotherapy respectively.*

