#### **11.4 Trial closure**

The treatment phase will be followed by a non-interventional follow up period which will continue for 8 weeks after the last participant completes protocol treatment.

For the purposes of the Research Ethics Committee approval, the study end date is deemed to be the date of last data capture. The expected end date is 01/02/2012.

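### Section 12.5 lists weeks 17 and 20 as two time-points, but they are one follow-up visit dated by cycles received; taken literally, the between-arm comparison is split by a post-randomisation factor

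*Protocol*

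**What the plan says.** Section 12.5 sets the between-arm strength analysis, under an intention-to-treat label: "change in leg muscle strength from baseline will be compared between trial arms at 9, 17 and 20 weeks". It then turns to quality of life, body composition, nutritional intake and fatigue: "Descriptive statistics will then be presented for the following measures at 9, 17 and 20 weeks".

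The rest of the protocol describes one follow-up visit:

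- The synopsis in Section 2.0 ties the date to cycles received: "17/20 week from start of chemotherapy assessments (3/4 cycles received".
- Section 9.5 has a single set of measures under "Follow up assessments (17 / 20 weeks from start of chemotherapy".
- Section 9.6 has one combined column for weeks 17 and 20, with one strength measurement in it, and its note says that "the timing of assessments will be standardised to treatment cycles".
- Section 11.4 says that follow-up "will continue for 8 weeks after the last participant completes protocol treatment".

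Secondary objective iii asks: "What is the rate of recovery or decline in these parameters following cessation of" 3–4 cycles of chemotherapy, and whether NMES influences it.

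**The concern.** Nobody is scheduled to be measured at both week 17 and week 20. If the arms are compared at each, the first comparison can contain only participants who received 3 cycles and the second only those who received 4. Cycles received is known only after randomisation: entry requires being scheduled for 3–4 cycles (Section 6.1), and Section 12.1 names no stratification factor that would fix the number in advance. Neither comparison is then the randomised comparison that the intention-to-treat label promises.

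Section 12.3 gives comparison of some secondary endpoints as the reason for having a control arm, and leg strength is the only measure that Section 12.5 sets out to compare between arms. At stake is whether the single planned between-arm comparison after treatment is made once, on everyone with data, or twice on fragments.

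**Working it through.** **1. Is it one visit?** Treatment ends at week 9 after 3 cycles and week 12 after 4 (Sections 9.3 and 9.4). Adding the 8 weeks of Section 11.4 gives 9 + 8 = 17 and 12 + 8 = 20. Both labels mean the same visit, 8 weeks after the end of treatment, which agrees with the single column in Section 9.6.

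**2. Who is left at follow-up?** Section 12.3 plans 26 NMES and 21 control participants and cites a local audit in which about 25% drop out before 3 cycles. Assuming that rate in both arms:

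- NMES: 26 × 0.75 = 19.5 (in line with the protocol's own target of 20 analysable)
- Control: 21 × 0.75 = 15.75

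**3. Precision of the pooled and split comparisons.** The protocol states no power or target effect for leg strength, so there is no figure of its own to reproduce. The standard error in SD units is √(1/n₁ + 1/n₂). The detectable difference below is from a two-sample t-test, two-sided 5%, 80% power. The share going on to cycle 4 is not given, so it is varied by assumption.

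| Comparison | NMES v control | SE (SD units) | Ratio to pooled | Detectable difference |
|---|---|---|---|---|
| Pooled visit | 19.5 v 15.75 | 0.339 | 1.00 | 0.98 SD |
| Half of participants | 9.75 v 7.875 | 0.479 | √2 = 1.41 | 1.43 SD |
| One third | 6.5 v 5.25 | 0.587 | √3 = 1.73 | 1.83 SD |
| Two thirds | 13.0 v 10.5 | 0.415 | √1.5 = 1.22 | 1.22 SD |

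The normal approximation, (1.96 + 0.84) × SE, gives 0.95 SD pooled and 1.34 SD for an even split, so the conclusion does not depend on the method.

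**4. Could the split also bias the result?** Only under further assumptions. Suppose NMES has no effect on strength, a standard normal fitness score decides who receives cycle 4, and fitness correlates 0.3 to 0.5 with strength change. If 60% of the NMES arm and 40% of controls go on to cycle 4, mean fitness in the 4-cycle groups is 0.386/0.6 = 0.64 and 0.386/0.4 = 0.97, a difference of −0.32. In the 3-cycle groups it is −0.97 and −0.64, again −0.32. Multiplying by the correlation gives a false difference of about −0.10 to −0.16 SD at both week 17 and week 20. If the shares are equal and selection works alike in both arms, the bias is zero.

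**5. Objective iii.** Section 9.6 schedules strength, body composition and activity at week 9 but not week 12. For a 4-cycle participant, week 9 comes before the week-10 cycle, and NMES continues to week 12. The change from week 9 to week 20 therefore includes a further cycle and further NMES; it is not purely change since cessation.

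**The case against.** The best defence is that listing 17 and 20 weeks is shorthand for the combined visit. Section 12.5 does not say that the arms will be compared within cycle groups, Section 12.6 plans no formal subgroup analyses, and a full analysis plan, not at hand here, is promised. That is a plausible account of intent. But Section 12.5 itself fixes the time-points, nothing in the protocol states pooling, and an analyst following the text would split. This is a rule stated wrongly, not a detail left for later.

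Two parts of the defence stand in full. The comparison was never powered, and even pooled it detects only a difference near 1 SD, so the loss of precision should not be overplayed. And Section 12.5 specifies change from baseline, not from week 9, so the objective iii point concerns how a result is labelled and is not an error in a specified analysis.

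A reader might infer that the 3-cycle and 4-cycle groups are sorted by tumour response or toxicity, and that the split is therefore biased. The documents do not support this: they do not say what decides cycle 4, and they give no figures by arm. A reader might also infer that objective iii should be answered in 3-cycle participants alone. Used to compare arms, that would condition on the same post-randomisation factor and drop participants whom the objective covers.

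**Conclusion.** The point holds at moderate severity. Section 12.5 contradicts the protocol's own visit design. Taken literally, it replaces one follow-up comparison with two in disjoint groups defined by cycles received, neither of which is the stated intention-to-treat comparison. Under 75% retention in both arms and an assumed even split, each has a standard error 1.41 times the pooled one and a detectable difference of about 1.43 SD instead of 0.98 SD; a one-third/two-thirds split gives ratios of 1.73 and 1.22. The loss of the randomised comparison and of precision needs no assumption about selection. Bias does, and it remains a possibility only.

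It would be tempting to conclude that pooling restores full intention to treat. It does not: under Section 11.3, participants who stop chemotherapy after 1 or 2 cycles are withdrawn and no further data are collected. Nor does the point reach the trial's main conclusion, since the adherence endpoint and its decision rule are assessed within the NMES arm.

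**What to change.** In Section 12.5, name two times in place of three, for both the strength comparison and the descriptive measures: week 9, and the follow-up visit 8 weeks after the end of chemotherapy (week 17 or 20). Then state that:

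- at each time there is one pooled comparison, by allocated arm, of all randomised participants with data;
- any results by cycles received are descriptive only;
- where change from week 9 to follow-up is reported for objective iii, for 4-cycle participants it includes cycle 4 and continued NMES, and the between-arm comparison is not restricted to 3-cycle participants;
- participants withdrawn after 1 or 2 cycles have no follow-up data, so the comparison is not full intention to treat.

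The cost is a wording change in Section 12.5, carried into the analysis plan. It needs no new visits, measurements or participants.

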#### Secondary objectives

- i) Is NMES a safe intervention to offer patients undergoing palliative chemotherapy?
- ii) To what extent does 3-4 cycles of palliative chemotherapy impact on leg muscle strength, body composition and physical activity levels in patients with NSCLC and can the use of NMES influence these changes?
- iii) What is the rate of recovery or decline in these parameters following cessation of 3–4 cycles of chemotherapy and can the use of NMES influence this?
- iv) What are patients' attitudes to the use of NMES during chemotherapy?

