## 4.0 Study design

An open randomised phase II study in patients with non-small cell lung cancer. 47 patients will be randomised to receive either palliative chemotherapy or palliative chemotherapy plus the NMES programme. Patients will be randomised with a 2:1 allocation ratio in favour of the NMES intervention arm.

A Fleming's one-stage design is applied to the experimental arm, with the proportion of patients completing NMES for 30 minutes, three times a week as the primary endpoint.

A control arm will be used to see what the change in activity is (muscle strength, body composition, physical activity, safety) in a similar population of patients having usual practice of palliative chemotherapy.

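### Section 12.5 gives step count no analysis, toxicity no final summary by arm and body composition no by-arm wording, so it answers objectives i to iii only in part

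*Protocol*

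**What the plan says.** Objective i in Section 3.0 asks: "Is NMES a safe intervention to offer patients undergoing palliative chemotherapy". Objective ii asks about chemotherapy's "impact on leg muscle strength, body composition and physical activity levels in patients with NSCLC and can the use of NMES influence these changes". Objective iii carries the same three measures past the end of treatment: "What is the rate of recovery or decline in these parameters following cessation of 3–4 cycles of chemotherapy", again asking whether NMES alters this.

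Section 4.0 states what the control arm is for: "A control arm will be used to see what the change in activity is (muscle strength, body composition, physical activity, safety". Section 12.3 is more reserved: "We have included a randomised control arm into this trial design in order to allow comparison of some secondary end points". Section 12.2.2 lists both step count and toxicity among the secondary outcomes.

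Beyond the primary endpoint, Section 12.5 sets out three things:

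- By intention to treat, "change in leg muscle strength from baseline will be compared between trial arms at 9, 17 and 20 weeks". This is the section's only between-arm comparison.
- A descriptive part, introduced by "Descriptive statistics will then be presented for the following measures at 9, 17 and 20 weeks", that covers quality of life, body composition, nutritional intake and fatigue. The body composition entry reads only "Change in body composition from baseline".
- Response to chemotherapy, described in each arm.

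Section 12.5 also says that a full SAP will follow. It is not available here.

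**The concern.** Leaving analytic detail to a SAP is normal. Here, though, the protocol gives its own list of what will be analysed, and that list does not match the objectives or the stated purpose of the control arm. Quality of life, fatigue and nutrition are listed although objectives i to iii do not name them. Step count, which objectives ii and iii do name, is absent, and so is toxicity. A SAP that followed Section 12.5 closely would carry the gap forward. One that departed from it would add analyses that the protocol had not specified.

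At stake is part of the case for phase III. The overall aim in Section 3.0 is to inform the feasibility and justification of that trial. The pilot's trend towards benefit included daily step count, and the lay summary says physical activity will be used to explore benefit. Leaving that measure without a stated analysis, in an open trial, leaves room for selective reporting.

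**Working it through.** **Setting the sections side by side**

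| Item | Objective (3.0) | Control-arm purpose (4.0) | Outcome (12.2.2) | Analysis in 12.5 |
|---|---|---|---|---|
| Leg strength | ii, iii | yes | yes | compared between arms |
| Body composition | ii, iii | yes | yes | descriptive, by-arm wording absent |
| Step count | ii, iii | yes | yes | none |
| Safety / toxicity | i | yes | yes | none |

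Of the four items that Section 4.0 gives for the control arm, one has a contrast, one is described and two do not appear. By-arm wording is used in Section 12.5 for response to chemotherapy but not for body composition.

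**Timing.** Section 12.5 names 17 and 20 weeks as if they were separate times. Sections 9.5 and 9.6 show one follow-up visit at week 17/20, and the synopsis ties the week to whether 3 or 4 cycles were received. This is 8 weeks after chemotherapy in both cases: 9 + 8 = 17 and 12 + 8 = 20, in line with the 8-week follow-up in Section 11.4. Analysing the two weeks separately would split each arm by number of cycles received, which is determined after randomisation.

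**Numbers available**

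- Section 12.3 requires 20 evaluable in the NMES arm. The one-sided normal approximation reproduces this: [(1.645 × 0.5 + 1.282 × 0.4) / 0.3]² = 19.8, so 20.
- Section 12.3 plans 26 NMES and 21 control participants with about 25% dropout. 26 × 0.75 = 19.5, about 20. 21 × 0.75 = 15.75, about 16, if the same dropout applies to controls (an assumption).
- Step-count recordings: at most 47 × 3 = 141. With 36 participants remaining after baseline, 47 + 2 × 36 = 119.

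**Precision of a between-arm estimate, in SD units**

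- SE of a difference in follow-up values = √(1/20 + 1/16) = 0.335.
- 95% half-width with t on 34 df (2.032): 0.68 SD.
- Change score, with equal SDs at baseline and follow-up and correlation r: 0.68 × √(2(1 − r)).
- Baseline-adjusted: 0.68 × √(1 − r²).

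The documents do not give r. I assume 0.6 and show 0.5 to 0.7.

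| r | Change score | Baseline-adjusted |
|---|---|---|
| 0.5 | 0.68 | 0.59 |
| 0.6 | 0.61 | 0.55 |
| 0.7 | 0.53 | 0.49 |

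The change score is the right comparator, because Section 12.5 already plans change from baseline. Setting 0.55 against the unadjusted 0.68 would overstate the gain.

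**The case against.** The strongest reply is that Section 12.5 promises a full SAP and never calls its list exhaustive, so silence on step count is incompleteness and not a decision to leave it unanalysed. Section 12.3 offers comparison of only some secondary end points. The trial is powered on the intervention arm alone, so describing unpowered outcomes is a legitimate choice in a phase II feasibility study. Nothing prevents body composition from being tabulated by arm. Toxicities are graded by CTCAE v3.0, recorded on the CRF and scheduled from baseline to follow-up. Adverse events are listed annually for the ethics committee and sponsor, and the IDMC reviews safety.

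Much of this stands. A reader might infer that the trial cannot answer objectives i to iii. The documents do not support that: strength is compared between arms at week 9 and at follow-up, which answers part of ii and iii, and safety has collection and review provisions elsewhere. A reader might also infer that the step-count data will go unused, or that the phase III decision depends on them. Section 12.5 does not say the first, and Section 12.3 ties the decision to adherence (15 or more of 20).

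What the reply does not remove is the mismatch itself. Section 12.3 says some end points, but Section 4.0 says which, and step count and safety are among them. Collection, interim review and annual listing are not a final summary by arm.

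**Conclusion.** The point holds as a misalignment. Section 12.5 leaves one of the three measures in objectives ii and iii without any analysis, gives no final toxicity summary by arm, and does not say that body composition is shown by arm. The objectives are incompletely answered, not unanswerable. Step count is the clearest gap. Body composition is the weakest, since by-arm tables would be consistent with the present text.

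A contrast with an interval is worth reporting although it would be imprecise: about ±0.55 SD baseline-adjusted (0.49 to 0.59 for r from 0.7 to 0.5), against ±0.61 SD for a change score. These figures assume 25% dropout in both arms, equal SDs over time and r = 0.6. They show what such an estimate could deliver, not a loss caused by the omission. No sample-size figure changes.

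**What to change.** In Section 12.5:

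- Report the baseline-adjusted between-arm difference with 95% CI for leg strength, lean mass (body and thighs) and mean daily step count. Label it exploratory estimation, with no powered test.
- Give it at two times: week 9, and the single follow-up visit 8 weeks after the end of chemotherapy (week 17 or 20 by cycles received).
- Add toxicity by arm, as maximum CTCAE grade per participant.
- Keep quality of life, fatigue and nutrition descriptive, and state that they are shown by arm.

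The cost is a few lines of text and a little more analysis of data already collected. The price in interpretation is that the intervals will be wide and must not be read as evidence of efficacy or of no effect.
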